#### Definition of the primary efficacy endpoint and event definitions

2.12.1

The primary efficacy endpoint is the proportion of patients with an mRS score ≤ 2, assessed at 16 weeks after treatment initiation.

Relapse event: Defined as the occurrence of new or worsening neurological or psychiatric symptoms attributable to NMDARE following an initial period of at least 2 months of clinical improvement or stabilization, accompanied by at least one of the following: (1) recurrence or an increase in anti-NMDAR antibodies in cerebrospinal fluid (CSF) or serum; (2) new or worsening abnormalities on brain MRI consistent with encephalitis; or (3) new or increased epileptiform activity on EEG. All relapse events must be reviewed and confirmed by an independent adjudication committee (6, 21, 27, 28).

Rescue treatment event: Defined as the initiation of any additional immunotherapy beyond the assigned study treatment due to insufficient clinical improvement, clinical deterioration, or life-threatening complications. This includes, but is not limited to, cyclophosphamide, bortezomib, tocilizumab. The decision to initiate salvage therapy is made by the treating physician and subsequently reviewed and confirmed by the independent adjudication committee (21, 29).

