#### Analysis methods for primary and secondary endpoints

2.12.2

For the primary endpoint, the comparison of the proportion of patients achieving mRS ≤ 2 at week 16 between treatment groups will be performed using a Cochran–Mantel–Haenszel test stratified by study center, with a two-sided significance level of 0.05. A logistic regression model adjusting for stratification factors and baseline covariates (e.g., age, baseline mRS) will be used as a supportive analysis.

For time-to-event endpoints, including relapse and salvage treatment events, Kaplan–Meier curves will be used to summarize event times, and event rates with 25%/75% quartiles will be calculated. The stratified log-rank test will be used for intergroup comparisons, and hazard ratios with 95% confidence intervals will be estimated using a Cox proportional hazards model, with stratification factors included as covariates.

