#### Analysis populations

2.12.4

The Intent-to-Treat (ITT) population was defined as all randomized patients who received at least one dose of the study drug. The Full Analysis Set (FAS) population was defined as patients who met the inclusion criteria and completed at least one efficacy assessment. The primary analysis will be performed on the ITT population. If the difference in key baseline characteristics or primary outcome between the FAS and ITT populations exceeds 5%, the primary analysis will additionally be performed on the FAS population.

For patients who withdraw from the study due to severe adverse events or other reasons, data after withdrawal will be handled using last observation carried forward (LOCF) in sensitivity analyses. For time-to-event analyses, such patients will be censored at the time of withdrawal under the non-informative censoring assumption.

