## Summary

3

Autoimmune encephalitis is a severe and potentially life-threatening condition associated with significant risks of disability. The recovery process for patients with severe manifestations can be prolonged and fraught with complications. While the number of patients accurately diagnosed with this condition is increasing, there are currently no approved pharmacological therapies and no data from randomized controlled trials to inform treatment. Consequently, treatment options are predominantly based on empiric opinion and clinical experience. First-line immunotherapies (steroids, plasma exchange and/or IVIG) with or without second-line immunotherapies (e.g., cyclophosphamide and rituximab) indicate that patients achieve ‘good’ outcomes (mRS score ≤2) in approximately 70% of patients with NMDARE, the most common subtype of AE. Nevertheless, a well-recognized problematic cohort that fails to improve with these interventions and requires ICU admission remains. This unmet need has prompted a search for additional therapies with different mechanisms of action. Owing to the severity of neurological deficits and substantial mortality observed in severe NMDARE, aggressive immune suppression targeting different aspects of humoral immunity is warranted. Sequential therapy consisting of BCDT (rituximab or ofatumumab) followed by daratumumab may provide a stronger suppression of humoral immunity by targeting both B cells and antibody-secreting plasma cells. This study is the first to investigate the efficacy of treatment with B-cell-depleting agents followed by daratumumab in achieving plasma cell depletion, reducing pathogenic antibody titres, and ultimately improving outcomes for patients with severe autoimmune encephalitis. The primary endpoints of the study is the proportion of patients with an mRS score ≤2. Although the mRS does not capture the diverse clinical manifestations of autoimmune encephalitis comprehensively, it has become the most widely utilized clinical outcome measure in stroke trials and has been applied to evaluate autoim mune encephalitis outcomes. Furthermore, through structured assessments, we aimed to collect data on memory function deficits and neuropsychological status related to the disease and explore the potential beneficial effects of daratumumab on these symp toms. By addressing these multifaceted aspects of the condition, this study contributes valuable insights into the management and treatment of AE.

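### Relapse and salvage exclude death but are reported as Kaplan–Meier event rates, so these rates modestly overstate the proportion of patients who had the event

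*Protocol article*

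**What the plan says.** Section 2.12.1 of the protocol article defines two time-to-event endpoints. Relapse is "Defined as the occurrence of new or worsening neurological or psychiatric symptoms attributable to NMDARE" after a period of improvement or stability, supported by an antibody, MRI or EEG finding. Rescue treatment, also called salvage, is "Defined as the initiation of any additional immunotherapy beyond the assigned study treatment", given "due to insufficient clinical improvement, clinical deterioration, or life-threatening complications". Death is part of neither definition.

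Section 2.12.2 fixes the analysis of both: "Kaplan–Meier curves will be used to summarize event times, and event rates with 25%/75% quartiles will be calculated". It continues: "The stratified log-rank test will be used for intergroup comparisons", with hazard ratios from a Cox model.

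Section 2.12.4 gives the only censoring rule. It begins "For patients who withdraw from the study due to severe adverse events or other reasons" and provides that in time-to-event analyses "such patients will be censored at the time of withdrawal under the non-informative censoring assumption". Section 2.12.3 adds restricted mean survival time as a sensitivity analysis if censoring is heavy.

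No section names death as an event, a competing event or part of a composite. The Summary (section 3) refers to "substantial mortality observed in severe NMDARE".

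**The concern.** A patient who has died can no longer relapse or start salvage therapy. Kaplan–Meier with death censored treats that patient as if the event could still have happened later, at the rate seen in survivors. The complement of the curve then estimates a risk in a hypothetical setting without death, not the proportion of randomised patients who had the event. The plan calls the quantity an event rate, and readers will take it as that proportion.

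There is also a question of interpretation for salvage. Its triggers include deterioration and life-threatening complications. A death without salvage is a treatment failure of the same kind, but it leaves the risk set without being counted. The hazard ratio for salvage therefore says nothing about such deaths and can mislead if it is read alone.

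**Working it through.** **Inputs.** Event definitions come from 2.12.1, the method from 2.12.2 and the 48-week horizon from Table 1. The article states no relapse, salvage or death rate and no power for these endpoints, so there is no figure of its own to reproduce. All rates below are assumptions.

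**1. Excess over the true proportion.** Let F be the true 48-week proportion with the event and D the proportion who die without it. Cause-specific hazards are constant, and cumulative over 48 weeks.

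- Total hazard: H = −ln(1 − F − D)
- Event hazard: λ₁ = H × F/(F + D)
- One minus Kaplan–Meier, deaths censored: 1 − exp(−λ₁)

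| F | D | H | λ₁ | 1 − KM | Excess over F |
|---|---|---|---|---|---|
| 20% | 5% | 0.2877 | 0.2301 | 20.6% | 0.6 points |
| 30% | 10% | 0.5108 | 0.3831 | 31.8% | 1.8 points |
| 30% | 15% | 0.5978 | 0.3986 | 32.9% | 2.9 points |

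**2. The same check from the reported side.** Suppose the curve reports 20%, and D* is the net 48-week death risk. Then λ₁ = −ln(0.80) = 0.2231 and λ₂ = −ln(1 − D*). The cumulative incidence is λ₁/(λ₁ + λ₂) × [1 − exp(−(λ₁ + λ₂))].

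| D* | Cumulative incidence | Excess of 1 − KM |
|---|---|---|
| 2% | 19.8% | 0.2 points |
| 5% | 19.5% | 0.5 points |
| 10% | 19.0% | 1.0 point |
| 15% | 18.5% | 1.5 points |
| 20% | 18.0% | 2.0 points |

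**3. Sensitivity to timing.** If every death came before any salvage, the cumulative incidence would be (1 − D*) × 20%. That is 19.0% at 5% deaths (excess 1.0 point) and 16.0% at 20% deaths (excess 4.0 points).

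**4. What the salvage analysis does not show.** Take the same salvage hazard in two arms (one minus Kaplan–Meier 20% in each) and net death risks of 15% and 5%.

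- Kaplan–Meier for salvage: 20% v 20%
- Cumulative incidence of salvage: 18.5% v 19.5%
- Salvage or death: 1 − 0.80 × 0.85 = 32% v 1 − 0.80 × 0.95 = 24%

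The salvage curves are identical although one arm has clearly more failures. Cumulative incidence of salvage alone does not show this either. It corrects the reported proportion, but the excess deaths appear only when deaths are displayed by arm or included in a composite.

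**The case against.** **The article never says that deaths are censored.** This is true. Its censoring rule covers withdrawals, and a fuller document might say more about death. But the article fixes the event definitions and the estimator, and followed as written they leave a death no other place. The point concerns the stated method, not a missing detail.

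**The bias is small.** This also stands. With 20% events and 5% deaths it is about half a point, and the remark on mortality in the Summary is a general one without a figure.

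**The tests are not wrong.** This stands too. Log-rank and Cox with deaths censored are valid for the cause-specific hazard. A salvage test that rejects at about its nominal level when salvage is equal and deaths differ is behaving correctly.

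**Stronger readings that a reader might infer, and that the documents do not support:**

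- *The arm with more deaths would look better on the salvage curve.* Under the constant-hazard model it looks slightly worse: with true salvage of 20% in both arms and deaths of 10% v 3%, one minus Kaplan–Meier is 21.2% v 20.3%.
- *Adding death to the endpoint would gain power.* That depends wholly on an assumed death difference in the same direction as salvage. With deaths equal at 3%, salvage 25% v 15% and 80 per arm, simulated unstratified log-rank power was 36% for salvage alone and 32% for the composite. These figures also leave out the planned stratification.
- *The planned quartiles will not be reached.* The article gives no relapse or salvage rate from which to judge this. The assumed week-16 mRS response rates are not a substitute.

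**Restricted mean survival time is already planned.** It uses the same censoring of deaths, so it does not resolve the point.

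**Conclusion.** The concern holds in a limited form. Applied as written, 2.12.2 yields Kaplan–Meier rates of relapse and salvage that exceed the proportions of patients who had those events whenever any patient dies first. Under constant hazards and assumed rates, the excess runs from about 0.6 points (20% events, 5% deaths) to about 3 points (30% events, 15% deaths). It is larger if deaths cluster early, and negligible if deaths are few.

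The planned between-group tests remain valid for the cause-specific hazard. Their limit is that a death without salvage does not count as failure, so they need to be read beside deaths by arm.

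The scope is narrow. Relapse and salvage are not in the secondary endpoint list of section 2.10, and the primary analysis of mRS ≤ 2 at week 16 is not touched by this point. The existence of the bias follows from the definitions and the method. Its size rests on death and event rates that the article does not give.

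**What to change.** In section 2.12.2:

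1. Report relapse and salvage event rates as Aalen–Johansen cumulative incidence, with death as a competing event, at fixed weeks (for example 16, 24 and 48) with 95% confidence intervals.
2. Keep the log-rank test and Cox model, label the Cox estimate a cause-specific hazard ratio, and present deaths by arm beside it.
3. Add salvage-or-death as a supportive analysis, with the two components shown by arm. The salvage definition in 2.12.1 can stay as it is.

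The cost is a few sentences of analysis wording and standard software. No new data collection is needed for deaths on study, because section 2.6 already follows serious adverse events for one year from treatment initiation or until withdrawal. The downside is small: the composite mixes two event types and gains nothing if deaths are balanced between arms, which is why it should be supportive and shown with its components.

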#### Methods for additional analyses

2.12.3

If the degree of censoring is high, a restricted mean survival time analysis will be performed as a sensitivity analysis to support the main estimator. For missing data in the primary endpoint, multiple imputation under the missing-at-random assumption will be applied, and sensitivity analyses will be conducted under alternative missing-data assumptions to assess the robustness of the primary outcome. In addition, sensitivity analyses will be performed under different response rate assumptions to evaluate the stability of the results.

#### Analysis populations

2.12.4

The Intent-to-Treat (ITT) population was defined as all randomized patients who received at least one dose of the study drug. The Full Analysis Set (FAS) population was defined as patients who met the inclusion criteria and completed at least one efficacy assessment. The primary analysis will be performed on the ITT population. If the difference in key baseline characteristics or primary outcome between the FAS and ITT populations exceeds 5%, the primary analysis will additionally be performed on the FAS population.

For patients who withdraw from the study due to severe adverse events or other reasons, data after withdrawal will be handled using last observation carried forward (LOCF) in sensitivity analyses. For time-to-event analyses, such patients will be censored at the time of withdrawal under the non-informative censoring assumption.

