**Study design:**

This multicenter, open-label, randomized controlled trial is conducted across 58 tertiary hospitals in China. Eligible participants are patients with severe AE especially NMDARE (mRS ≥ 3 points and neuropsychiatric manifestations inadequate to symptomatic treatment) post first-line immunotherapy. A total of 200 patients will be randomized at a 2:2:1 ratio into three groups. 80 patients will receive B-cell depleting agent (anti-CD20 mAb ofatumumab) followed by anti-CD38 mAb daratumumab, 80 patients will receive B-cell depleting agent ofatumumab alone, and 40 receive repeated IVIG or plasmapheresis.

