### Study intervention

2.5

The RADIA trial includes a 14-day screening period used to determine participant eligibility. Prior to this screening period (specifically, within 90 days before randomization), individuals must have received first-line treatments such as high-dose intravenous corticosteroids, intravenous immunoglobulin (IVIg), and/or plasmapheresis. Importantly, participants who have received at least 2 doses of FcRn antagonist efgartigimod are still eligible for enrollment. The treatment period of the RADIA trial begins at the time of randomization. Participants will be randomized to receive either BCDT followed by daratumumab, BCDT, or repeated IVIG/PE.

The strategy of BCDT refers to multiple sclerosis. Anti-CD20 ofatumumab is administered subcutaneously at a dose of 20 mg at weeks 0, 1, and 2 (loading doses), followed by 20 mg every 4 weeks from week 4 to week 24 (maintenance doses: weeks 4, 8, 12, 16, 20, 24).

Daratumumab will be administered intravenously on the day after each ofatumumab administration. The daratumumab dosing schedule is: 8 mg/kg at weeks 0, 1, 2, and 4 (loading dose), followed by 4 mg/kg at weeks 8, 12, 16, 20, and 24 (maintenance dose). Pre-medication (corticosteroids, antihistamines, and antipyretics) is required before each daratumumab infusion to minimize infusion-related reactions.

In this study, each administration of daratumumab is defined as one treatment cycle. A total of 9 administrations are planned at weeks 0, 1, 2, 4, 8, 12, 16, 20, and 24, resulting in a total treatment duration of approximately 24 weeks. The effects of this daratumumab regimen will be evaluated throughout the study period. Laboratory tests will be required before each dose of the study drug to determine if any dose adjustments are necessary. During the study, patients should receive comprehensive supportive care as appropriate, aligned with their institutional guidelines. Necessary concomitant medications or treatments to ensure adequate supportive care, such as anti-epileptic drugs, may be prescribed. The following concomitant medications are strictly prohibited during the study: natalizumab, cyclosporine, mitoxantrone, mycophenolate mofetil, and azathioprine.

For adolescent patients aged 12–18 years, the doses of study drugs are consistent with the dosing regimen for adult patients. The safety and efficacy of ofatumumab in this age group have been established, and the dose is identical to that used in adults (22–25).

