### Sample size calculation

2.11

The sample size was calculated based on the primary endpoint, defined as the proportion of patients achieving a modified Rankin Scale (mRS) score ≤ 2 at 16 weeks after treatment initiation. Due to the absence of robust published data from randomized controlled trials in this specific patient population, the initial response rate assumptions were derived from limited retrospective studies and clinical experience in patients with severe autoimmune encephalitis.

Under the primary assumption of a 90% response rate in the BCDT followed by daratumumab group and a 70% response rate in the BCDT alone group, with a two-sided significance level of 0.05 (*α* = 0.05) and 80% power (*β* = 0.20), the estimated required sample size was 64 patients per group. After accounting for a 10% dropout rate, approximately 80 participants were estimated for each of the two active comparison groups. For the third group (repeated IVIG/PE), given the anticipated difficulty in recruitment and its role as an exploratory reference arm, the sample size was set at 40 patients. Thus, the total planned sample size was 200 patients.

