By addressing these multifaceted aspects of the condition, this study contributes valuable insights into the management and treatment of AE.

This trial is conducted solely in China, which may limit the generalizability of findings to other regions with different ethnic backgrounds, healthcare systems, or treatment protocols. Future studies should aim to include a more diverse population to enhance external validity.

Additionally, the open-label design may introduce performance and detection bias, particularly in the assessment of subjective outcomes. To minimize this limitation, several strategies have been implemented. Outcome assessors are independent from the treatment team and blinded to treatment allocation. In addition, all outcome assessments are video recorded and reviewed by an additional independent neurologist, with discrepancies resolved by a third adjudicator, thereby enhancing inter-rater reliability and objectivity. A standardized assessment protocol is applied across all study sites to ensure consistency. Furthermore, the primary endpoint (mRS ≤ 2) is a well-established functional scale with relatively high objectivity.

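### The primary analysis set labelled ITT is a modified ITT: it needs at least one dose in an open-label trial, and no set of all randomised patients is stated

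*Protocol article*

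**What the plan says.** Section 2.12.4 (Analysis populations) defines two sets.

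- ITT: "The Intent-to-Treat (ITT) population was defined as all randomized patients who received at least one dose of the study drug". Then: "The primary analysis will be performed on the ITT population".
- FAS: "The Full Analysis Set (FAS) population was defined as patients who met the inclusion criteria and completed at least one efficacy assessment". It enters only on a condition: "If the difference in key baseline characteristics or primary outcome between the FAS and ITT populations exceeds 5" per cent, the primary analysis is repeated on the FAS in addition.

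Neither set contains everyone randomised. The Abstract states the setting: "This multicenter, open-label, randomized controlled trial is conducted across 58 tertiary hospitals in China". The Summary accepts that "the open-label design may introduce performance and detection bias, particularly in the assessment of subjective outcomes".

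Four other places bear on the point:

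- Section 2.5 (Study intervention): "The treatment period of the RADIA trial begins at the time of randomization". Both ofatumumab arms have ofatumumab at week 0, and daratumumab follows the next day in the combination arm.
- Section 2.6, Table 1: ofatumumab and daratumumab are marked from week 0; IVIG/PE is marked at weeks 4, 8 and 12.
- Sections 2.10 and 2.12.1: the 16 weeks of the primary endpoint are counted from the start of treatment.
- Section 2.11: the powered comparison is combination against ofatumumab alone. The IVIG/PE arm has 40 patients, "given the anticipated difficulty in recruitment and its role as an exploratory reference arm".

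**The concern.** Randomisation makes the groups comparable as randomised. Receiving a dose comes later. Without blinding, the patient, the family and the physician know the arm by then, so refusal, withdrawal or a change of plan before the first dose can depend on it. Removing those patients can leave groups that differ in prognosis, and the primary test then no longer has a guaranteed type I error.

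Other safeguards in the article do not cover this. The blinded video review in section 2.6 protects the scoring of outcomes, not the choice of who is analysed. Multiple imputation in section 2.12.3 deals with missing endpoints and is not said to bring back patients who are outside the set.

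The dose condition may also differ by arm, because the article does not say what counts as a dose of study drug in each one.

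**Working it through.** **1. The plan's own figures.** The set definition carries no number. The nearest planning figure is 64 per group in section 2.11 (90% v 70%, two-sided 0.05, power 80%). The pooled formula gives

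n = [1.96·√(2·0.8·0.2) + 0.8416·√(0.9·0.1 + 0.7·0.3)]² / 0.2² = (1.109 + 0.461)² / 0.04 = 61.6, so 62.

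That is within 2 patients of 64. I take from this section only the 70% rate and the 80 patients per arm.

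**2. What the dose condition means in each arm.**

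| Reading | Consequence |
|---|---|
| First ofatumumab injection counts | Same entry event, at week 0, in both powered arms |
| Study drug means daratumumab | Combination patients given ofatumumab only drop out; the ofatumumab-alone arm has no counterpart |
| Table 1 taken literally for IVIG/PE | Patients lost in weeks 0–3 drop out of that arm only |

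The second reading is possible because section 2.5 defines a treatment cycle by daratumumab administrations and section 2.6 then speaks of study drug cycles. The third rests on one table row. Section 2.5 gives no IVIG/PE dates, and its statement that treatment starts at randomisation has to be reconciled with that row.

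**3. Illustration for the powered pair.** The documents give no undosed rate, so these inputs are assumed: no true effect, 70% in both arms, 80 randomised per arm, x undosed in one arm only, and those patients would respond at rate r.

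- Observed rate in that arm: p₁ = (56 − x·r)/(80 − x), where 56 = 0.7 × 80.
- Spurious difference: d = p₁ − 0.70.
- Pooled rate: p̄ = [(80 − x)·p₁ + 56]/(160 − x). Standard error: SE = √{p̄(1 − p̄)[1/(80 − x) + 1/80]}.
- Two-sided type I error: 1 − Φ(1.96 − d/SE) + Φ(−1.96 − d/SE). This is a normal approximation that ignores stratification by centre.

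| x (share) | r | p₁ | d, points | Type I error |
|---|---|---|---|---|
| 2 (2.5%) | 30% | 55.4/78 = 71.0% | +1.0 | 0.052 |
| 2 (2.5%) | 0% | 56/78 = 71.8% | +1.8 | 0.057 |
| 4 (5%) | 30% | 54.8/76 = 72.1% | +2.1 | 0.060 |
| 4 (5%) | 0% | 56/76 = 73.7% | +3.7 | 0.080 |
| 8 (10%) | 30% | 53.6/72 = 74.4% | +4.4 | 0.094 |
| 8 (10%) | 0% | 56/72 = 77.8% | +7.8 | 0.193 |

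With r = 70%, d is zero and the error stays at 0.05 for every x. The same holds if both arms lose the same share and kind of patient.

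**4. Direction.** Dropping likely failures raises the rate of the arm that loses them. At the planned 90%, losing four failures gives 72/76 = 94.7% (+4.7 points), and losing four responders gives 68/76 = 89.5% (−0.5). Early failures lost from the IVIG/PE arm would flatter that arm and so work against the antibody regimens. The sign therefore depends on which arm loses patients and who they are.

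**The case against.** The strongest defence is that the powered comparison is barely touched. Both of its arms begin with the same subcutaneous injection at week 0, and the treatment period starts at randomisation. Few patients should go undosed, and a combination patient who declines daratumumab after ofatumumab would plausibly stay in the set. The possible week-4 asymmetry concerns only an arm that the plan calls exploratory. This largely stands: a material bias in the primary contrast is not shown. It does not justify the definition, because near-symmetry depends on a reading of study drug that the article does not state.

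A reader might go further on three points, and the article does not support any of them.

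- *The expected recruitment difficulty in the IVIG/PE arm means refusal after allocation.* Section 2.11 uses it only to explain the size of that arm. It could equally mean consent declined before randomisation, which affects no analysis set.
- *Study drug, taken literally, removes the whole IVIG/PE arm.* That is plainly not intended. The gap is one of wording.
- *The 5% rule lets the FAS replace the ITT.* The FAS analysis is additional and the ITT stays primary. The FAS has no dose requirement, so it can even include undosed patients with one assessment. The weakness is only that the observed outcome helps decide whether the analysis is run, which is minor.

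It might also be said that a journal article condenses a fuller protocol. That would excuse an omission, but here the article states a definition.

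**Conclusion.** The point holds as one of principle that is cheap to correct. The primary set is a modified ITT under the ITT label, in an open-label trial, with no stated analysis of all randomised patients. What is lost is the guarantee of randomisation. It would be wrong to infer that the primary result will be badly biased.

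The illustration gives about 2 to 4 points and a type I error of about 0.06 to 0.08 at 5% undosed. That rests on three assumptions: losses in one arm only, a response rate of 0 to 30% in those lost, and 70% otherwise. Across the scenarios run (up to 10% undosed) the error goes from 0.05 to 0.19. With few undosed patients, or similar losses in both arms, the effect is slight. It is probably small between the ofatumumab arms if the shared first injection is the qualifying dose. For the IVIG/PE arm, exclusion would be one-sided only if Table 1 is taken literally. That arm is exploratory in section 2.11, although section 2.10 words the primary objective against standard immunotherapy.

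**What to change.** 1. Define ITT as all randomised patients, analysed in the arm assigned whether or not dosed, and use it for the primary analysis.
2. Count the 16 weeks of the primary endpoint from randomisation. Start of treatment is undefined for an undosed patient, so item 1 cannot be applied without this.
3. Collect the week-16 mRS of undosed patients, or impute it under the missing-data plan in section 2.12.3.
4. Rename the dosed set modified ITT or treated set, state for each arm what counts as first study treatment, and keep the set for sensitivity and safety analyses.
5. Reconcile the IVIG/PE row of Table 1 with the statement in section 2.5 on when treatment begins.
6. Run the FAS analysis always, as a sensitivity analysis, and delete the 5% trigger.

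The cost is protocol and SAP wording plus follow-up of probably few patients. Enrolment is planned to December 2026, so the change is still feasible. There is some dilution. At 90% v 70% with 80 per arm, power is 0.893. If 2.5% of the combination arm are undosed and respond at 70% or 30%, that arm's rate becomes 0.975 × 90% + 0.025 × r = 89.5% or 88.5%, and power is 0.874 or 0.829. At 5% undosed the rates are 89% and 87%, and power is 0.852 or 0.749. The loss is slight when undosed patients are few, which is also a reason to keep the interval from randomisation to first treatment short.

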#### Inclusion criteria

2.2.1

The patient inclusion criteria were as follows:Aged 12 years and older.Diagnosis of autoimmune encephalitis targeting neural surface antigen, predominantly NMDARE.At least 3 days of high-dose methylprednisolone pulse therapy (500–1000 mg) and IVIG (0.4 g/kg/day for 5 consecutive days), at least 5 sessions of plasma exchange or immunoadsorption, or at least 2 doses of FcRn antagonist efgartigimod have been used.mRS score ≥3 and neuropsychiatric manifestations inadequate to symptomatic treatment.Provision of informed consent by the participant or legal guardian.Negative pregnancy test for women of childbearing potential (up to 2 years postmenopause).

After providing informed consent, participants will enter a 14-day screening period. For individuals unable to provide consent owing to the severity of their condition, a legally authorized representative (or an equivalent individual as specified by local law) may provide informed consent, ensuring compliance with local regulations.

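### LOCF, the only specific sensitivity method named for withdrawn patients, has no fixed direction of bias and does not test the missing-at-random assumption behind the primary analysis

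*Protocol article*

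**What the plan says.** Two places in the protocol article deal with missing outcomes.

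- **Section 2.12.3 (Methods for additional analyses)** sets the main method: "For missing data in the primary endpoint, multiple imputation under the missing-at-random assumption will be applied". It then promises that "sensitivity analyses will be conducted under alternative missing-data assumptions to assess the robustness of the primary outcome", without naming any.
- **Section 2.12.4 (Analysis populations)** sets a rule for withdrawals. It opens with "For patients who withdraw from the study due to severe adverse events or other reasons" and states that "data after withdrawal will be handled using last observation carried forward (LOCF) in sensitivity analyses". The next sentence censors such patients at withdrawal in the time-to-event analyses. I therefore read the LOCF rule as covering the scale outcomes, including the primary mRS endpoint.

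Three further facts matter. The endpoint is a single binary status (mRS 2 or less), "assessed at 16 weeks after treatment initiation" (section 2.12.1). Eligibility requires "mRS score ≥3 and neuropsychiatric manifestations inadequate to symptomatic treatment" (section 2.2.1), so every patient starts as a non-responder. Table 1 has mRS scored weekly to week 8 and then at weeks 12 and 16.

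**The concern.** A sensitivity analysis for withdrawals should show whether the primary conclusion survives if missing-at-random is wrong, and in particular if patients who left did worse than similar patients who stayed. LOCF does not put that question. It assumes that nothing changes after the last visit, in a trial where patients start disabled and are treated in the expectation of recovery.

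It can err in two opposite ways:

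- A patient who leaves early is fixed as a failure, although recovery may have been under way.
- A patient who reached mRS 2 and then left is counted as a week-16 success, although the response may not have lasted.

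Which error dominates in each arm depends on who leaves and when, so LOCF is neither conservative nor anti-conservative by design. It also treats the filled-in value as observed and so understates uncertainty.

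At stake is the robustness check, not the primary estimate. A LOCF result that disagrees with the primary result could reflect withdrawal timing alone. One that agrees would not show how poor the missing outcomes would have to be to overturn the conclusion.

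**Working it through.** **Inputs from the protocol.** Section 2.11 assumes a "90% response rate in the BCDT followed by daratumumab group" and 70% with BCDT alone, hence a planned difference of 20 points. It uses two-sided alpha 0.05, 80% power, 64 per group, 10% dropout and 80 per group after inflation.

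**The plan's own figure.** The pooled two-proportion formula gives n = [1.96 × √(2 × 0.8 × 0.2) + 0.8416 × √(0.09 + 0.21)]² / 0.20² = 61.6, so 62 per group. This is within 2 of the stated 64, so the 90% v 70% basis is sound for what follows.

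**Assumptions, not in the protocol.** How withdrawals split between arms, and how many leavers had already responded at their last visit.

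**Case A: leavers would have reached their arm's planned rate at week 16.** Let p be the arm's response rate, d the share withdrawing before week 16, and f the share of the leavers' eventual responders already at mRS 2 or less when last seen. Then

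LOCF rate = p(1 − d) + d × f × p.

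f = 0 means that all leave before responding, f = 1 that all leave after. f = 0.5 corresponds to response accruing linearly to week 16 with withdrawals spread evenly. The combination arm is given first.

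| d (%) | f | LOCF rates (%) | Difference (points) | Shift from 20 |
|---|---|---|---|---|
| 10 / 10 | 0 / 0 | 81.0 v 63.0 | 18.0 | −2.0 |
| 10 / 10 | 0.5 / 0.5 | 85.5 v 66.5 | 19.0 | −1.0 |
| 10 / 10 | 1 / 1 | 90.0 v 70.0 | 20.0 | 0.0 |
| 10 / 10 | 0 / 1 | 81.0 v 70.0 | 11.0 | −9.0 |
| 10 / 10 | 1 / 0 | 90.0 v 63.0 | 27.0 | +7.0 |
| 15 / 5 | 0.5 / 0.5 | 83.25 v 68.25 | 15.0 | −5.0 |
| 15 / 5 | 0 / 0 | 76.5 v 66.5 | 10.0 | −10.0 |
| 5 / 15 | 0.5 / 0.5 | 87.75 v 64.75 | 23.0 | +3.0 |
| 5 / 15 | 0 / 0 | 85.5 v 59.5 | 26.0 | +6.0 |

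With equal d and f in both arms the difference is 20 × [1 − d(1 − f)], which at d = 10% lies between 18 and 20 points.

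**Case B: leavers are truly non-responders at week 16, but LOCF credits responses at the planned rates.** The true difference is 90(1 − d) − 70(1 − d), each with its own arm's d, and LOCF reports 90 − 70 = 20.0.

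- 10% / 10%: true 81.0 − 63.0 = 18.0, so LOCF overstates by 2.0 points.
- 15% / 5%: true 76.5 − 66.5 = 10.0, so LOCF overstates by 10.0 points.

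**What this does to the check.** With 80 per arm, an unstratified two-proportion test has 89% power at 90% v 70%. It has 72% at 81% v 63% and 37% at 81% v 70%. In the last case the LOCF check would more often than not miss significance, although in Case A the true difference is 20 points.

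**What a tipping-point analysis would add (illustration).** Suppose 8 of 80 are missing in each arm and completers give 65/72 v 50/72, pooled z-test p = 0.0018. Count all 8 missing combination patients as failures. If 4 of the 8 missing BCDT-alone patients succeed, 65/80 v 54/80 gives p = 0.046. If 5 succeed, 65/80 v 55/80 gives p = 0.068. That locates the limit. A single LOCF result does not.

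**The case against.** The strongest reply is that this is a secondary check. The LOCF sentence is explicitly limited to sensitivity analyses. Multiple imputation covers a withdrawn patient with no week-16 mRS like any other missing case, and the frequent mRS visits give the imputation model something to work with. All of this stands. A reader might infer that LOCF distorts the primary estimate, or that it is the only method applied to withdrawals. The text supports neither.

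Second, section 2.12.3 already promises analyses under alternative assumptions, and their detail may properly sit in an analysis plan not shown here. This also stands: it cannot be said that the trial lacks a better check. But LOCF is not an omitted detail. It is a stated commitment and the only specific method named for these patients, so it can be judged as written.

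Third, the larger shifts rest on imbalance that the protocol does not predict. Its only dropout figure is 10%, with no difference between arms, and on that figure with equal timing the shift is 0 to 2 points. It would be wrong to infer that LOCF moves the result by several points in general. Imbalance is nevertheless possible: the trial is open-label, only one arm adds nine daratumumab infusions (section 2.5), and section 2.8 lists laboratory, cardiac and infection grounds for ending participation.

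Fourth, the rule should not be read as one for severe adverse events alone, since it covers other reasons too. Finally, the tipping illustration uses unstratified tests rather than the centre-stratified Cochran–Mantel–Haenszel test of section 2.12.2, so it shows the principle and predicts nothing.

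**Conclusion.** The point holds as a modest one. LOCF is a weak choice as the only named sensitivity method for withdrawals: the direction of its bias depends on who leaves and when, and it does not probe missing-at-random in an interpretable way. At 10% withdrawal with equal amount and timing, the LOCF difference departs by 0 to 2 points from the true one under either case worked above. With marked imbalance in amount or timing it departs by about 5 to 10 points in either direction, and by less when the imbalance is milder. Those larger figures rest on assumed withdrawal patterns and on the planned 90% and 70% rates. They concern the LOCF sensitivity estimate only. The multiple-imputation primary estimate does not change.

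**What to change.** In section 2.12.4, replace LOCF as the sensitivity analysis for withdrawals with delta-adjusted (tipping-point) multiple imputation. Vary the response odds of withdrawn patients separately in each arm. Start at missing-at-random, which reproduces the primary analysis, and run to the point where all withdrawals for adverse events or worsening count as non-responders. Report the combinations at which the primary conclusion would change.

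This also gives content to the unnamed alternative assumptions in section 2.12.3. Because multiple imputation is already planned, it needs no new data and no change to the primary analysis. The only cost is slightly more analysis work.
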